### 2.6. Sample Size

As this is a feasibility/pilot study, no sample size to detect between group differences was calculated. The study may provide preliminary data for the calculation of a sample size for a future full-scale evaluation. We aim to recruit 2 fully outdoor ELC settings, 2 satellite ELC settings, and 2 traditional ELC settings.

A minimum of 10 children per ELC setting will be recruited. Two practitioners and one headteacher/manager will be recruited from each ELC setting.

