The progression criteria for **RQ2** are also conditional upon which traffic light criteria are achieved regarding retention rates within **RQ1**. The number of retained children will undergo matching based on their propensity score. 

The traffic light criteria for **RQ3** are based on what we determine to be sufficiently acceptable to carry out analysis of the outcome data to detect an effect if one does exist. Outcome measures that can detect a signal in effect will be considered for progression to the next stage of evaluation subject to meeting the other progression criteria. These will also be considered alongside the number of barriers mentioned related to the measures in the interviews and feedback from parents/carers. The outcomes and their measurement tools are outlined in Table 4.

The traffic light criteria for **RQ4** are based on the extent to which analysis of M&E tools can be standardised across ELC settings. It is important for researchers to maximise the use of M&E tools that are already in place to reduce the burden on practitioners, increasing the likelihood of optimal participation and supporting evaluation capacity.

Finally, the progression criteria for **RQs 5 and 6** are based on the qualitative findings informed by NPT. If participants feel they have agency and resources to support outdoor play and learning and there are no major barriers associated with the study design, then progression to a powered effective evaluation will be possible after consultation with the research steering group.

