#### 2.8.2. Measurement Tools

Table 4 demonstrate the measurement tools that will be used at each timepoint. Although one timepoint is sufficient for determining the feasibility of collecting the data by researchers, there are other uncertainties that can be addressed by using two timepoints. Collecting data at both timepoints will allow us to assess the acceptability of the study design by estimating the burden of taking part in the measurements for children and also the ELC educators supporting the data collection. Additionally, we will be able to estimate potential programme effects and determine which child health outcomes should be taken forward as primary and secondary outcomes in a powered effectiveness evaluation.

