1. To what extent are the intended participants ***recruited*** to the study and are they ***retained***?	Recruitment: *ELC Settings* GREEN: at least 30% of contacted ELC settings express a willingness to participate. AMBER: 10 to 29%. RED: less than 10% of contacted ELC settings respond. *Participants* GREEN: fully outdoor ELC settings, at least 50% of eligible children return a signed consent form. At satellite and traditional ELC settings, at least 25% of eligible children return a signed consent form. AMBER: at least 50% of fully outdoor ELC settings achieve their 50% recruitment target. At least 50% of satellite and traditional ELC settings achieve their 25% recruitment target RED: Amber target is not achieved	GREEN: Strong indication to use the same recruitment process in full effectiveness evaluation. AMBER: Indication that recruitment process might work, but should be discussed with research steering group. RED: Indication that recruitment process needs serious revision before full effectiveness evaluation.	Data collected on eligible ELC settings and participants, response rates, and non-response rates.	Based on recruitment and retention rates of past feasibility studies in UK early years settings (Barber et al., 2019; Kipping et al., 2019; Malden et al., 2019).
	Retention GREEN: 80% or more participant retention rate. AMBER: 50–79% participant retention rate. RED: less than 50% participant retention rate.	GREEN: Strong indication to use the same recruitment process in full effectiveness evaluation. AMBER: Indication that recruitment process might work, but should be discussed with research steering group. RED: Indication that recruitment process needs revision before full effectiveness evaluation.		

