2. To what extent can propensity score matching based on multiple treatment groups be suitably applied within this context?	GREEN: 80% or more enrolled children suitably matched based on propensity scores. AMBER: 50–79% enrolled children matched. RED: less than 50% enrolled children matched.	GREEN: Strong indication that matching children based on their propensity score is a reliable comparison method to be used in a powered effectiveness evaluation. AMBER: Indication that the matching method might work in an effectiveness evaluation; however, it should be considered alongside other criteria such as the level of missing data. RED: The study design method needs careful consideration before being used again.	Determine the suitability of the covariates collected in the demographic survey are sufficient to calculate reliable propensity scores for matching.	We consider 80% to be achievable if the criteria regarding retention in RQ1 is successful.
3. What ***outcomes*** should be included in a future impact evaluation and how should they be measured?	GREEN: 70% or more measures are returned fully completed at baseline and follow-up. Outcome measures are able to identify a change from baseline to follow-up and a difference in effect between intervention and comparison groups (positive or negative). No major acceptability issues during educator interviews or via parent feedback. AMBER: Outcome measure completion rate of 60% or more. An indication that there may be a difference in effect but insufficient data to determine definitively. Three or four major acceptability issues raised by interviewees or through parent feedback; however, mitigating strategy identified. RED: Less than 60% of outcome measures completed. Major acceptability issues raised regarding measurement methods with no possible mitigation strategy.	GREEN: Strong indication to proceed with the outcome measurement methods. AMBER: Medium indication to proceed. Recommend discussing the measurement methods with research steering group. RED: Indication of doubt as to whether to proceed. Measurement methods should be discussed with steering group, taking into consideration findings from RQ6 and whether different measurement tools might be better suited to detect an effect in outcomes.	Baseline and follow-up outcome measures. Feedback from parents in activity diary. Process evaluation interviews with ELC educators.	We consider 70% completion rate sufficient to carry out analysis.

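### The RQ3 GREEN criterion asks outcome measures to show a between-group difference in a study not sized to detect one, and a complete, acceptable measure with a null result fits no colour

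*Protocol article*

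**What the plan says.** Section 2.6 is explicit about size: "As this is a feasibility/pilot study, no sample size to detect between group differences was calculated". The same section sets the recruitment target: "We aim to recruit 2 fully outdoor ELC settings, 2 satellite ELC settings, and 2 traditional ELC settings", and "A minimum of 10 children per ELC setting will be recruited". That gives about 20 children per model as a floor.

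Table 3, RQ3, sets three conditions for GREEN:
- at least 70% of measures fully completed at both timepoints;
- no major acceptability issues;
- "Outcome measures are able to identify a change from baseline to follow-up and a difference in effect between intervention and comparison groups", in either direction.

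AMBER lowers completeness to 60% and asks for an indication of a possible difference, allowing that the data may be too few to settle it. RED is defined by completeness below 60% and by acceptability problems that cannot be mitigated. It says nothing about effect.

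Section 2.8.1 adds: "Outcome measures that can detect a signal in effect will be considered for progression to the next stage of evaluation", subject to the other criteria and alongside interview and parent feedback. Section 2.8.2 says that with two timepoints the team can estimate programme effects and "determine which child health outcomes should be taken forward as primary and secondary outcomes in a powered effectiveness evaluation". Section 2.8 lists a null effect, next to positive and negative ones, among the results to be recorded for RQ3.

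**The concern.** The study disclaims any sizing for group differences, then makes such a difference part of its strongest progression grade and a basis for choosing the next study's outcomes. Whether a measure shows a difference in two settings against two says little about whether it is a good measure. A sound tool for an outcome that truly responds can easily show nothing at this size, and a poor one can show a difference because two settings happen to differ. The RQ3 grade is meant to inform the choice of primary and secondary outcomes for the powered evaluation, so a noisy clause in it matters.

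The colour bands also fail on a likely result: a measure that is complete and acceptable but shows no difference.

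**Working it through.** **Inputs from the protocol.** Two settings per model and at least 10 children per setting (2.6), so n = 20 per model. GREEN retention is 80% ("GREEN: 80% or more participant retention rate", Table 3), so 16 of 20. GREEN completeness is 70%, so 14 of 20. Follow-up is at 5 weeks (2.2).

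**Assumptions.** The protocol gives no significance level, effect size, SD or intracluster correlation (ICC), so there is no figure of its own to reproduce. I take a two-sided 5% test, standardised differences d of 0.3 and 0.5, baseline-to-follow-up correlations r of 0.3 to 0.8, and ICC of 0.05 and 0.10.

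**1. Power at follow-up, one exposure model v traditional, clustering ignored.** Two-sample t test with noncentrality d/√(2/n).

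| n per group | d = 0.3 | d = 0.5 | d with 80% power |
|---|---|---|---|
| 20 | 15% | 34% | 0.91 |
| 16 | 13% | 28% | 1.02 |
| 14 | 12% | 25% | 1.10 |

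**2. Power on change scores.** Table 1 plans matching combined with difference-in-differences, which uses the baseline value. The SD of change is √(2(1 − r)) in units of the outcome SD, so the effect becomes d/√(2(1 − r)). At 20 v 20:

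| r | SD of change | d = 0.3 | d = 0.5 |
|---|---|---|---|
| 0.3 | 1.18 | 12% | 26% |
| 0.5 | 1.00 | 15% | 34% |
| 0.7 | 0.77 | 22% | 51% |
| 0.8 | 0.63 | 31% | 68% |

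Only a moderate effect with a high correlation is detected more often than not.

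**3. False signals from clustering.** With 10 children per setting the design effect is 1 + 9 × ICC, and the error of a naive 5% test is roughly 2[1 − Φ(1.96/√design effect)].
- ICC 0.05: design effect 1.45; 1.96/√1.45 = 1.63; about 10%.
- ICC 0.10: design effect 1.90; 1.96/√1.90 = 1.42; about 16%.

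Simulating a t test with two settings of 10 per group gives the same rounded values. A cluster-level test of 2 v 2 settings (2 degrees of freedom) at ICC 0.05 has power of only 8% at d = 0.3 and 13% at d = 0.5.

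**4. If a signal need not be significant.** The standard error of the observed d at 20 v 20 is √(2/20) = 0.316. With no true effect, an observed difference of at least 0.2 in either direction occurs with probability 2[1 − Φ(0.2/0.316)] = 53%. With a true effect of 0.2, the observed sign is wrong with probability Φ(−0.632) = 26%. A looser reading of the clause does not rescue it.

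**5. The colour bands.** Take a measure with at least 70% completeness, no major acceptability issue and no difference between groups.
- GREEN: fails, because it requires a difference.
- AMBER: fails, because it requires an indication of a difference.
- RED: fails, because neither the completeness nor the acceptability condition is met.

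No colour applies, although section 2.8 foresees null results.

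**The case against.** A reader might infer that outcomes will be kept or dropped by chance. The protocol does not say that. RED has no effect clause, so a null result never makes a measure RED. AMBER allows for insufficient data and leads to discussion with the steering group, as RED does. Section 2.8.1 says that measures with a signal will be considered; it does not exclude the rest, and Table 3 does not say that every measure must pass. The bands are described as levels of acceptability, not strict thresholds. All of this stands, and it limits the consequence to missing GREEN.

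Two further inferences fail. One is that inflated pilot effects would size the next study: section 2.6 says only that the study may supply preliminary data, and section 2.9.3 refers to summary statistics. The other is a 40% chance of at least one false signal (1 − 0.95^10), which assumes five measures with two independent contrasts each. Table 4 shows four child tools at both baseline and week 5, giving eight contrasts (1 − 0.95^8 = 34%). Section 2.8.2 confines follow-up height and weight to two of the three models, giving seven (30%). The contrasts also share one control group, so they are not independent.

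It is also fair that Table 3 names no significance test, that 10 per setting is a minimum, and that using baseline values can raise power. Steps 2 and 4 allow for the first and third. More children in the same two settings per model would not remove the setting effect. The inconsistency between section 2.6 and the RQ3 criteria remains, as does the gap in the bands.

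**Conclusion.** The point holds in a bounded form, and the plan should be changed. The RQ3 effect clause asks for something that section 2.6 says the study was not sized to show. Under the assumptions above, a measure of an outcome that truly responds by 0.3 SD would meet the clause about 12–31% of the time. At 0.5 SD the figure is 26–68%, above half only when the baseline correlation is about 0.7 or more. A naive test would also signal a difference where none exists about 10–16% of the time at ICC 0.05–0.10. For small to moderate effects the clause thus reflects sampling error more than the quality of the measure. Very large effects, around 0.9 SD or more, could be seen if clustering is ignored.

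The consequence is that responsive measures will usually miss GREEN, not that they will be discarded. The missing colour for a complete, acceptable, null measure follows from the text alone and needs no assumption.

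**What to change.** Delete the effect clause from the RQ3 GREEN and AMBER criteria in Table 3 and the signal sentence in section 2.8.1. Reword section 2.8.2 so that pilot effect estimates no longer determine the choice of outcomes.

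Grade each measure on completeness, acceptability and measurement properties: floor and ceiling effects, SD, and baseline-to-follow-up correlation. A complete, acceptable measure with a null result can then be GREEN, which closes the gap.

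Choose primary and secondary outcomes for the powered evaluation from the existing Theory of Change and stakeholder work (section 2.1). Report group differences with 95% confidence intervals as descriptive only, with no role in progression.

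The cost is the wording of one table row and two sentences, with no extra participants or data collection. The downside is that the pilot no longer ranks outcomes by observed effect.

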## Data Availability

The quantitative and qualitative data collected will be held in an anonymised format in a UK Research Data Repository. The study’s results will be available to participants, healthcare professionals, the public, and other interested groups via a PhD thesis and Open Access journal articles.

## Appendix A. Interview Guide for Semi-Structured Interviews

**Table ijerph-19-07461-t0A1:**

Assessing the Acceptability of Programme and Trial Methods	Purpose of Question	Normalisation Process Theory Component
1. What health and wellbeing benefits do you think children acquire from attending nature-based ELC? - To what extent do you think there could be any possible harms or disadvantages from attending nature-based ELC?	Address participant’s views regarding implementation of the programme, identify whether participant’s views match with those from the EA workshops and findings in the literature. Can help direct data collection for full-scale evaluation.	***Coherence*** (e.g., how easy is the programme to describe, do participants believe the programme has a clear purpose, who does the programme benefit, how does it fit with the overall goals of early years provision?)
2. In what way do you believe outdoor play and learning is part of early years provision? To what extent do you believe you and your colleagues have sufficient support and resources (e.g., training, staff numbers, physical resources, etc.) to provide outdoor play and learning to the best of your ability? - Do you consider providing outdoor play and learning to be an important aspect of your job as an early years educator? - Is there anything you would improve?	Address implementation aspects of the programme, what is working and what is not. Support recommendations to stakeholders regarding how programme can be improved.	***Cognitive participation*** (e.g., are participants committed to providing the programme, do participants believe that providing the programme is a good use of their time?) ***Collective action*** (e.g., do participants believe they are sufficiently trained to provide the programme, do they have the resources they require, is it compatible with existing work practices?)
3. Thinking about continued future implementation of outdoor play and learning, are there any factors that might influence how you and your colleagues deliver outdoor play and learning? - To what extent do you feel capable of modifying outdoor play and learning provision to meet your nursery’s needs?	Identify contextual factors that influence the implementation of the programme.	***Reflexive Monitoring*** (e.g., participants are able reflect and critique the programme.)
4. Did the study recruitment process have any impact on the daily operations of your nursery? Were there more absences than usual during the study implementation period?	Assess the acceptability of the study methods.	***Coherence*** (i.e., are educators understanding of why the trial design methods have been used?) ***Cognitive participation*** (i.e., were educators supportive of the recruitment methods?) ***Collective action*** (i.e., did the study design have any impact on usual practice?) *Reflexive monitoring* of the trial methods is ongoing throughout the study through educator feedback and as part of the interviews.
5. What are your views on the data collection methods that were carried out during the study implementation period? - Was the use of activity monitors and height and weight scales too intrusive? Did children behave differently because of them? - Did the presence of an external researcher doing observations significantly influence the delivery of the programme or how children and staff interacted?	Assess the acceptability of data collection methods. Identify which methods can be taken forward to a full-scale evaluation.	***Coherence*** (i.e., do participants understand why these data collection methods are being used, how they might contribute to future implementation of the programme?) ***Cognitive action*** (i.e., were educators prepared to assist in the data collection methods, were children happy to participate?) ***Collective action*** (i.e., did educators believe they were skilled enough to support data collection, were they happy to share current monitoring and evaluation practices?) ***Reflexive monitoring*** (i.e., did participants believe that the outcomes the measurement tools were assessing important for programme implementation?)

## Appendix B. Play Observation Protocol (Adapted from Loebach and Cox 2020; Litlle, 2010)

**Table ijerph-19-07461-t0A2:**

Variable	Code
Event	Play event number
Participant	Unique ID
Play type	(1) Physical; (2) Exploratory; (3) Imaginative; (4) Play with rules; (5) Bio/nature; (6) Expressive; (7) Restorative; (8) Digital; (9) Non-play
Risky behaviour/play	(1) Heights; (2) Speed; (3) Dangerous tools (4) Dangerous elements (5) Rough and tumble (6) Exploring alone (7) Impact (8) Vicarious
Peer interaction	(1) Solitary; (2) Parallel; (3) Cooperative; (4) Onlooking; (5) Conflict; (6) Unoccupied
Adult interaction	(1) No adult presenting/observing; (2) Observing; (3) Participating; (4) Directing; (5) Restricting; (6) Other
Environmental interaction	(LN) Loose natural; (FN) Fixed natural; (LM) Loose manufactured; (FM) Fixed manufactured
Play communication	(1) Play; (2) Environment; (3) Peer-social; (4) Adult-social; (5) Cowabunga!; (6) Wayfinder; (7) Instructive; (8) Care; (9)Permission seeking; (10); Self-talk; (11) Conflict
Interaction with coder	Yes; No
Open Coding	Descriptive texts
